#### Missing data.

Our team will work to keep missing data to a minimum. We will program our case report forms in REDCap to prompt respondents to answer all items if they attempt to submit the form without responding to all items. To ensure the voluntary nature of participation, we will program REDCap such that the measures can still be submitted with responses blank/missing. For all variables, we will assess the degree and pattern of missing data to see whether missing data elements can be inferred from other responses. Full information maximum likelihood (FIML) procedures will be used for any student with missing covariate information [39]. FIML methods use all the observed data and produce estimates of the parameters by integrating over the missing data.

#### Data and trial monitoring.

Consistent with expectations of the study sponsor, the study did not include a data and safety monitoring committee. The confidentiality and privacy of data will be monitored carefully by the study principal investigators and statisticians on a monthly basis throughout the study. In addition, the Office of Research Compliance at the study site will conduct periodic audits to ensure compliance with federal, state, and institutional regulations. Further, the Institutional Review Board will oversee the study implementation to ensure compliance with regulations.

#### Analyses for Aims 1–3: Evaluation of HOPS vs. TAU/WL and comparison of HOPS-ST to HOPS-RT.

*Hypothesis 1:* Students in HOPS-ST will demonstrate significantly fewer OTMP skills deficits and homework problems and will show significantly better academic performance at post-treatment compared to students in TAU-WL*Hypothesis 2:* Students in HOPS-RT will demonstrate significantly fewer OTMP skills deficits and homework problems and will show significantly better academic performance at post-treatment compared to students in TAU-WL.*Exploratory:* Examine whether the effects of HOPS-ST and HOPS-RT differ at post-treatment and follow-up.

A linear mixed-effects modeling approach will be used to examine intervention effects at post-treatment. An intent-to-treat approach to data analysis will be applied, including all children with baseline data in the analytic model. Under this approach, we will examine differences between students in HOPS (for HOPS-ST and HOPS-RT separately) vs. TAU-WL (as well as for students in HOPS-ST vs. HOPS-RT) by fitting a multilevel model in which students are nested within schools. In addition to including an indicator variable for the treatment condition, we will include covariates that explain variation at the student and school levels. To explore the sustainability of the intervention effect, we will examine how both means and slopes (rates of change) vary from baseline to 6-month and 12-month follow-up using regression analyses. Changes in mean and slope reflect variations in the magnitude of effect and pace of change during different phases of the study.

Because the efficacy of HOPS will be evaluated on three different domains of outcome measures (organizational skills, homework performance, academic achievement), we will use a Bonferroni-adjusted significance level to correct for multiple comparisons within each domain. As a result, the significance level will be adjusted to.025 per domain for the two measures of organizational skills (COSS-P, COSS-T), the two measures of homework performance (HPC, HPQ-T), and the two measures of academic achievement (APS, academic grades).

Power calculations were based on the following design parameters: *N = 30* schools (20 assigned to HOPS, 10 assigned to TAU); ICC = 0.04 (based on [4]); α=0.025  (reflecting the Bonferroni corrected significance level to accommodate multiple testing of two outcomes for each outcome domain); and $R^{\text{2}}=\text{0}.\text{6}\text{0}$ at the student and school level (which is the proportion of variation in outcomes explained by student and school-level covariates). Based on initial projections, we expected to enroll 8 students per school for a total of 240 participants (216 with 15% attrition), which would be sufficient to identify a minimal detectable effect size (MDES) of 0.41. Because of recruitment challenges primarily due to barriers related to the COVID-19 pandemic, we adjusted these projections to an average of 4.5 students/school for 30 schools for a total of 135 participants (122 with attrition). This sample size will result in a MDES of 0.48 with adequate power (80%). Based on prior research by [name] and colleagues [4], the MDES for primary outcomes in our study is well within the range of expected effect sizes.

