#### Random assignment of students in HOPS schools to school or research provider.

Students randomly assigned to the HOPS condition will be randomized once again to receive HOPS from either a school provider or research provider (on a 1:1 basis). The sequence of assignment of students in the HOPS condition to the school or research provider will be determined by a separate computer-generated list of random identification numbers overseen by the team statistician. Caregivers and teachers will be informed about study assignment after caregiver consent and child assent is provided.

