### Research settings

The study will be conducted in Philadelphia, PA greater metropolitan region. Our team will purposely recruit schools that are highly diverse in subsidized lunch rates of the schools and racial and ethnic composition of the students to maximize generalizability. Our team will attempt to recruit schools with varying levels of urbanicity (i.e., rural, suburban, and urban). We expect the racial and ethnic minority composition across schools to range from 15% to 99% and subsidized lunch rates to range from 15% to 100%. For each school, we plan on recruiting one or two school providers to implement the HOPS intervention.

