#### Analyses for Aim 6: Association of fidelity, engagement, working alliance to outcomes.

Our plan is to evaluate the extent to which provider intervention fidelity, student and caregiver engagement, and provider-student working alliance are associated with outcomes for participants in HOPS using multiple linear regression models. We will determine the proportion of variance in the outcome that is explained by the implementation factors, as assessed using adjusted R^2^ measures. Additionally, we will formally test the significance of the estimated coefficients to identify which implementation factor(s) are predictive of changes in the outcome measures.

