## Discussion

The main purpose of the study is to evaluate the effectiveness of the HOPS intervention when provided under authentic practice conditions by professionals working in the schools attended by enrolled students. School providers will receive training and technical support that is commonly offered when attempting to implement an evidence-based program in their schools, in contrast to more intensive consultation and coaching that is often provided through research trials (see [8]). In addition, the study will examine the effectiveness of HOPS when provided in schools by a limited number of study team members who work across multiple schools, which is similar to how the prior large-scale RCT of HOPS was conducted [4]. The study design will enable our team to explore differences in the effectiveness of HOPS when offered by school and research team members and variations in effectiveness related to differences in intervention content and process fidelity, student-provider working alliance, and student and caregiver engagement, as well as the cost associated with intervention implementation.

Strengths of the study include the in-depth monitoring of intervention fidelity by school and research providers, including both content and process fidelity, and the assessment of student and caregiver engagement in the intervention. The assessment of school provider fidelity will provide valuable information about how HOPS is implemented in authentic practice settings, factors contributing to variable implementation, and the association of fidelity to student outcomes. Another strength of the study is the analysis of factors that may contribute to variable effects of intervention, including severity of child symptoms of ADHD, oppositional defiant behavior, internalizing symptoms, as well as family socioeconomic factors, including caregiver level of education and the level of neighborhood disadvantage for participating families (i.e., Area Deprivation Index). Additional strengths of the study are the examination of variables that might account for the impact of HOPS on child academic outcomes and the analysis of the costs of implementing the program in authentic school settings.

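### Aim 6 tests implementation factors by ordinary regression that ignores shared schools and providers, and the school-only model cannot capture research providers who span schools (Aims 2 and 3, not Aim 1)

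*Protocol article*

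**What the plan says.** All references are to the protocol article.

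- **Analyses for Aims 1–3.** HOPS-ST versus TAU-WL, HOPS-RT versus TAU-WL, and HOPS-ST versus HOPS-RT are all estimated "by fitting a multilevel model in which students are nested within schools", with a treatment indicator and student- and school-level covariates. No provider effect is named. The accompanying power statement has one clustering input, a school-level ICC of 0.04.
- **Discussion.** HOPS-RT is delivered "by a limited number of study team members who work across multiple schools".
- **Research settings.** School providers are different: "For each school, we plan on recruiting one or two school providers to implement the HOPS intervention".
- **Analyses for Aim 5.** Moderators are tested inside the mixed models of Aims 1–3.
- **Analyses for Aim 6.** Fidelity, engagement and working alliance are related to outcomes "using multiple linear regression models". The results are to be tested: "we will formally test the significance of the estimated coefficients to identify which implementation factor(s) are predictive". No school or provider clustering is mentioned.

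**The concern.** Two students treated by the same provider share that provider's skill and style. The introduction itself says that effectiveness depends substantially on provider fidelity and alliance, so a provider variance of exactly zero would sit badly with the trial's rationale.

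This matters in two places.

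**Aim 6.** The analysis set is the treated students, about 90 of the 135, clustered in 20 schools and in providers. Ordinary regression treats their residuals as independent. That is wrong even on the trial's own school ICC of 0.04. It matters most for predictors that vary mainly between providers or schools, because predictor and residual then share the same clusters. Implementation factors could be declared predictive too often.

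**HOPS-RT contrasts.** A research provider's students are spread over several schools. A school random effect describes correlation within a school, not between students in different schools who share a provider. Hypothesis 2 (the replication claim, tested at 0.025) and the Aim 3 comparison could therefore report standard errors that are too small.

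**Working it through.** **Inputs from the document.** 30 schools (20 HOPS, 10 TAU); 4.5 students per school; 135 enrolled, 122 after attrition; ICC 0.04; R² 0.60 at both levels; α 0.025 (two-sided assumed); 1:1 split of HOPS students, so about 45 HOPS-ST, 45 HOPS-RT and 45 TAU.

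**Assumed, because not given.** Number of research providers k, and provider ICC ρ (share of total outcome variance).

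**1. Reproduce the stated MDES of 0.48 (school clustering only).** For one provider arm against TAU with n = 122/30 = 4.07 per school:

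- School part: 0.04 × 0.40 × (1/20 + 1/10) = 0.0024.
- Student part: 0.96 × 0.40 × 2/(10 × 4.07) = 0.0189.
- Variance 0.0213, SE 0.146.
- MDES = (2.368 + 0.855) × 0.146 = 0.470, with 28 df. Power at 0.48 is 81.6%.

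This agrees with the stated figure to within 2 points of power, and it contains no provider term.

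**2. Add a provider variance to HOPS-RT versus TAU.** Take ρ out of the student variance in the HOPS-RT arm, scale it by 1 − R² = 0.40, and add 0.40ρ/k. For k = 4, ρ = 0.05:

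- Variance = 0.0024 + 0.384/40.7 + 0.364/40.7 + 0.020/4 = 0.0258, SE 0.161.
- Ratio to the school-only SE: 0.161/0.146 = 1.10.
- Size of the 0.025 test: 2 × P(t₂₈ > 2.368/1.10) = 0.040.
- MDES: 0.470 × 1.10 = 0.518.

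Over k = 2–8 and ρ = 0.01–0.10 the SE ratio runs from 1.01 to 1.38, the size from 0.026 to 0.096, and the MDES from 0.475 to 0.647. These MDES values keep 28 df. With few providers the true df are smaller, so they are lower bounds.

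**3. Simulate the planned school-only mixed model** (20 + 10 schools, 4–5 students each, nominal 0.025):

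| k | ρ | HOPS-RT vs TAU: true SD / model SE | size | HOPS-RT vs HOPS-ST: size | HOPS-ST vs TAU: size |
|---|---|---|---|---|---|
| 3 | 0 | 0.221/0.223 | 0.022 | 0.015 | 0.023 |
| 3 | 0.02 | 0.240/0.223 | 0.031 | 0.040 | 0.027 |
| 3 | 0.05 | 0.254/0.224 | 0.038 | 0.050 | 0.022 |
| 3 | 0.10 | 0.285/0.226 | 0.076 | 0.098 | 0.021 |
| 5 | 0 | 0.215/0.223 | 0.015 | 0.019 | 0.020 |
| 5 | 0.02 | 0.233/0.224 | 0.025 | 0.027 | 0.021 |
| 5 | 0.05 | 0.252/0.225 | 0.033 | 0.041 | 0.016 |
| 5 | 0.10 | 0.266/0.227 | 0.043 | 0.067 | 0.020 |

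The last column shows no inflation of the primary contrast.

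**4. Aim 6, ordinary regression, by simulation** (4,000 runs per cell; 90 treated students in 20 schools; one school provider per school and one of k research providers serving each school; school ICC 0.04; nominal 0.05). Columns give the share of predictor variance lying between providers. Each cell shows true SE / OLS SE, then size.

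| k | ρ | share 0 | share 0.5 | share 1 |
|---|---|---|---|---|
| 3 | 0 | 1.01, 0.053 | 1.02, 0.050 | 1.05, 0.058 |
| 3 | 0.02 | 1.00, 0.046 | 1.05, 0.059 | 1.11, 0.072 |
| 3 | 0.05 | 1.01, 0.048 | 1.11, 0.077 | 1.18, 0.097 |
| 3 | 0.10 | 1.01, 0.049 | 1.15, 0.085 | 1.30, 0.129 |
| 5 | 0 | 1.01, 0.047 | 1.01, 0.049 | 1.05, 0.055 |
| 5 | 0.02 | 1.01, 0.048 | 1.05, 0.060 | 1.08, 0.066 |
| 5 | 0.05 | 1.02, 0.050 | 1.08, 0.069 | 1.17, 0.089 |
| 5 | 0.10 | 1.01, 0.050 | 1.12, 0.074 | 1.22, 0.105 |

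**5. Hand check for Aim 6.** With 4 research providers there are 4 clusters of 45/4 = 11.25 students and 20 school-provider clusters of 45/20 = 2.25. The size-weighted cluster is (4 × 11.25² + 20 × 2.25²)/90 = 6.75. With outcome ICC 0.10 and a wholly provider-level predictor, the design effect is 1 + 5.75 × 1 × 0.10 = 1.58. The SE factor is √1.58 = 1.26 and the size about 0.12, in line with the simulation.

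**The case against.** **This is detail for the analysis plan.** An article may leave out degrees of freedom, covariate lists and extra random effects. That stands for the absent provider-type term in Aim 6, which is not an error in itself. It does not stand for the models: the article names a different, single-level model for Aim 6 after keeping the mixed model for Aim 5, and it names the nesting for Aims 1–3 beside a delivery structure that does not fit it.

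**The size is assumed.** This stands. If the provider ICC is near zero, or there are many research providers, the inflation of Aims 2 and 3 is negligible; with 5 providers and ρ = 0.02 the Aim 2 size equals its nominal 0.025. Results also depend on whether ρ is taken as a share of total or of covariate-adjusted variance.

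**A reader might infer that all of Aims 1–3 fails.** The document does not support that. School providers number one or two per school, so they nearly coincide with the cluster already modelled, and the simulated size for HOPS-ST versus TAU is 0.016–0.027.

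**A reader might infer that HOPS-RT students are analysed as independent.** They are not: the school effect is in the model. Only the correlation that crosses schools is missed.

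**A reader might infer that Aim 6 predictors belong wholly to the provider, doubling the variance.** The measurement sections speak against this. Fidelity is coded in six sessions per participant, student engagement is rated for each student over sessions, and alliance is reported for each student–provider pair. The between-provider share is therefore somewhere below 1. A design effect near 2 would also need the research-provider cluster size of 11.25 applied to everyone, whereas half the sample is in clusters of about 2.25.

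**A few research providers might be treated as fixed.** This is a legitimate choice, but it narrows the conclusion to those providers, and the article states no such limit.

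**Conclusion.** The point holds in limited form and should be addressed.

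The firmest part is Aim 6. The stated regression drops a level that the trial uses elsewhere. From the stated school ICC of 0.04 alone the effect is small, about 1.05 on the standard error of a provider-level predictor. With an assumed provider ICC of 0.02–0.10 and 3 or 5 research providers, the 5% test has size of about 0.07–0.13 for a predictor wholly at provider level, 0.06–0.085 if half its variance is there, and no inflation for purely within-provider variation. Aim 6 is exploratory, but it is to be tested formally.

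The second part is qualified. Under the same assumptions the 0.025 test has simulated size 0.025–0.076 for Aim 2 and 0.027–0.098 for exploratory Aim 3. The direction follows from any positive provider variance, but whether it is material cannot be settled from the document. Aim 2 is the only hypothesis-testing aim at risk; the primary Aim 1 contrast is not.

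**What to change.** 1. **Aim 6.** Replace multiple linear regression with the mixed model of Aims 1–3, with random effects for school and provider, or use cluster-robust standard errors with a small-sample correction. Adjust for baseline outcome and provider type, so that a fidelity difference between school and research providers is not read as an effect of fidelity.
2. **HOPS-RT versus TAU, and HOPS-ST versus HOPS-RT.** Add a provider random effect for treated students only (crossed with school for research providers, none in TAU) with Satterthwaite or Kenward–Roger degrees of freedom, at least as a sensitivity analysis. Otherwise, state that inference is limited to these particular research providers.
3. **Reporting.** Give the number of research providers and show the HOPS-RT MDES over a range of provider ICCs.

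The cost is analysis code and wording. Providers complete attendance, engagement and alliance records on their students, so the student–provider link should already exist. The statistical price is wider intervals. With only three or four research providers, the provider variance rests on two or three degrees of freedom, may be estimated at zero, and could make the HOPS-RT intervals much wider. That is why the provider term is proposed for HOPS-RT at least as a sensitivity analysis, while the Aim 6 change is recommended outright.

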**Aim 1:** Evaluate the difference between HOPS-ST and TAU-WL on improvement in proximal outcomes (organization skills, homework performance) and distal outcomes (academic performance) at post-treatment (4-months after baseline) and explore the intervention’s sustainability (6 and 12-months after baseline). This aim will enable our team to determine the effectiveness of HOPS when provided by school professionals. We hypothesize that students in the HOPS-ST group will demonstrate significantly fewer OTMP skills deficits and homework problems and will show significantly better academic performance at post-treatment compared to students in TAU-WL. In addition, we expect the benefits of HOPS-ST to be maintained at follow-up.**Aim 2:** Examine the effectiveness of HOPS-RT in relation to TAU-WL. This aim will enable our team to replicate the findings of the [name] et al. [4] trial. We hypothesize that students in the HOPS-RT group will demonstrate significantly fewer OTMP skills deficits and homework problems and would show significantly better academic performance at post-treatment compared to students in TAU-WL. In addition, we expect the benefits of HOPS-ST to be maintained at follow-up.**Aim 3:** Explore differences in effect for HOPS-ST and HOPS-RT at post-treatment and follow-up.**Aim 4:** Explore mechanisms of action, specifically whether improvements in OTMP skills and homework performance mediate the effect of HOPS on improvements in academic performance.**Aim 5:** Explore whether student grade level, severity of organization problems, severity of ADHD, oppositional defiant behavior, and internalizing symptoms, and student medication status at baseline moderate the effect of HOPS on outcomes.**Aim 6:** Explore the extent to which treatment fidelity, student engagement, parent engagement, teacher engagement, and provider-student working alliance predicts outcomes for students in HOPS.**Aim 7:** Estimate the cost of providing HOPS under authentic practice conditions in schools.

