#### Collection of outcome data.

Outcome data for students in HOPS and TAU-WL will be collected at baseline and post-treatment (about 4 months after baseline). Follow-up data will be collected 6 months after baseline for students assigned to the HOPS condition. In addition, follow-up data will be collected 12 months after baseline for students in HOPS who remain in their school of enrollment the following school year. We will not collect 6-month and 12-month follow-up data for students in TAU-WL because of ethical concerns about further delaying the delivery of HOPS to those in the control group. However, we will collect post-treatment outcome data after students in the TAU/WL condition receive the HOPS program. Treatment fidelity, student engagement, and parent engagement will be assessed for participants in the HOPS condition during the intervention period. Provider-student working alliance will be assessed after the intervention period. Severity of organization problems, ADHD symptoms, disruptive behavior symptoms, and anxiety symptoms, as well as school organizational factors that may contribute to intervention implementation, will be assessed at baseline. (See Fig 3 for the study plan and flow diagram and see Fig 1 for a list of measures and the timelines for administering measures).

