### Recruitment

Two primary methods will be used to recruit schools. First, emails will be sent to the principals of schools serving students in grades 6–8 located in the large metropolitan area in which the study will be conducted. The selection of schools will be inclusive of districts across the region to achieve balance across subsidized lunch rate levels of the schools (low [0%−30%], middle [31%−60%], and high [61%−100%]). In addition, there will be an intentional effort to recruit schools in urban, suburban, and rural areas. Second, emails will be sent to principals of schools from districts in which we have previously conducted research or those referred to us by school administrators or other researchers. Approval will be obtained from the school principal, school superintendent, and school board (as necessary) prior to conducting research in the school. In addition, principals will be asked to identify one or more school providers to implement the HOPS intervention. School provider(s) must provide consent to participate in the study for the school to be enrolled in the study. Once all approvals and consents are obtained from school professionals, the school will be randomly assigned to a study condition (HOPS vs. TAU/WL).

Students will be referred to the study by their classroom (general education) teachers. School principals will identify the specific strategies to be used in convening teachers, informing them about the study, and obtaining referrals. Teachers will be informed that referral of a student to the study indicates their willingness to complete forms for outcome evaluation. The pool of teachers selected for inclusion in the referral process will be asked to nominate students from their general education classroom: (a) who are struggling the most with OTMP skills, (b) whose OTMP skill deficits interfere with their academic performance, and (c) who have at least one caregiver who speaks English. Each teacher who agrees to participate will complete a nomination form for each referred student for the purpose of determining student eligibility.

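### The exploratory sustainability analysis reads HOPS students' change from baseline as effect, with no untreated comparator after about 4 months, so a faded benefit could look maintained

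*Protocol article*

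**What the plan says.** All places are in the protocol article.

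- **Contrast.** Under Analyses for Aims 1–3, sustainability is explored as follows: "we will examine how both means and slopes (rates of change) vary from baseline to 6-month and 12-month follow-up using regression analyses". The next sentence gives the interpretation: "Changes in mean and slope reflect variations in the magnitude of effect and pace of change during different phases of the study".
- **Who is measured.** Under Collection of outcome data, both arms are assessed at baseline and at about 4 months. After that, "Follow-up data will be collected 6 months after baseline for students assigned to the HOPS condition", and at 12 months only those HOPS students who are still in their school of enrollment the next school year. For the control arm: "We will not collect 6-month and 12-month follow-up data for students in TAU-WL because of ethical concerns". TAU/WL students are next assessed after they have received HOPS.
- **Who is enrolled.** Under Recruitment, teachers nominate students "who are struggling the most with OTMP skills". Under Student participants, eligibility rests on the four interference items of the COSS-T. The COSS-T total is also an outcome (Outcome measures).
- **What is expected.** Under Study purpose and aims, Aim 1 says: "In addition, we expect the benefits of HOPS-ST to be maintained at follow-up". Aim 2 repeats the sentence.

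**The concern.** The effect of HOPS at a given time is the difference between HOPS students and what untreated students would have scored at that time. After post-treatment the trial has no untreated students. A change from baseline within HOPS therefore adds together three things: any remaining effect, regression to the mean in students chosen for poor status, and ordinary maturation over 6 or 12 months. The protocol reads this sum as size of effect.

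At stake is the follow-up message. If the effect seen at 4 months had faded, scores could still be better than at baseline and be reported as benefits maintained. The 12-month mean also comes from a narrower group than the post-treatment mean, because students who leave their school are not assessed. A difference between those two means may then reflect who is left rather than change in the same students.

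**Working it through.** The protocol gives no figure for this analysis, so there is none to reproduce. The check has four steps.

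**1. What can be estimated when** (from Collection of outcome data)

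| Time | HOPS | TAU/WL | Effect versus TAU/WL |
|---|---|---|---|
| Post-treatment, about 4 months | measured | measured, untreated | estimable, randomized |
| 6 months | measured | not collected | not estimable |
| 12 months | only those still in school | not collected | not estimable |

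**2. Possible size of regression to the mean.** The protocol gives neither a screening cut-off nor a retest correlation, so these are assumptions: the worst 10%, 20% or 30% are selected, under a normal model in population SD units. With p the fraction selected and c the cut-off, the selected group lies λ = φ(c)/p from the mean: 1.75, 1.40 and 1.16 SD. Expected improvement without any effect is

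(correlation of screen with baseline − correlation of screen with follow-up) × λ.

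- *Baseline score is the screening score* (first correlation 1, second r between 0.6 and 0.9). Smallest: (1 − 0.9) × 1.16 = 0.12 SD. Middle: (1 − 0.7) × 1.40 = 0.42 SD. Largest: (1 − 0.6) × 1.75 = 0.70 SD.
- *Baseline separate from the screen.* Correlation falling from 0.85 to 0.70 with 30% selected: 0.15 × 1.16 = 0.17 SD. Falling from 0.80 to 0.60 with 10% selected: 0.20 × 1.75 = 0.35 SD. Equal correlations: 0.

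As a yardstick only, the protocol's stated detectable effect is 0.48 SD.

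**3. Chance of a significant improvement from baseline when no effect remains.** The protocol expects 122 students after attrition. At 2:1, with equal numbers per school, that is 122 × 2/3 ≈ 81 in HOPS and about 41 in HOPS-ST. I use a one-sample t-test on change, two-sided at 0.025 (sidedness is assumed), with r = 0.7, so that the SD of change is √(2 × 0.3) = 0.77. Clustering by school is ignored.

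| Artefact | 81 HOPS | 41 HOPS-ST |
|---|---|---|
| 0.2 SD | 52% | 26% |
| 0.3 SD | 88% | 56% |
| 0.4 SD | 99% | 83% |

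**4. Does the choice of anchor matter?** A simulation used 4,000 replicates with 81 HOPS and 41 TAU/WL students, worst 20% selected, r = 0.7, and a true effect of 0.5 SD at post-treatment and exactly 0 at follow-up.

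| Mean change | Baseline is the screen | Separate, correlated baseline |
|---|---|---|
| HOPS, baseline to follow-up | 0.42 SD better | 0.29 SD better |
| HOPS, post-treatment to follow-up | 0.50 SD worse | 0.50 SD worse |
| TAU/WL, baseline to post-treatment | 0.42 SD better | 0.30 SD better |

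The baseline-anchored change was significant in 99.8% and 88% of replicates. Change from post-treatment shows the loss, and the TAU/WL change recovers the artefact. The simulation contains no maturation.

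**The case against.** The strongest reply is that the sentence should not be read as a two-point test. It speaks of means and slopes, the next sentence refers to different phases of the study, and Data collection and management plans summary tables that include post-treatment means. A model with a separate post-treatment segment would show a decline, and that segment would be largely free of regression to the mean. The analysis is also labelled exploratory, Hypotheses 1 and 2 are confined to post-treatment, and maintenance is an expectation with no decision rule. This stands, and it limits the point. It does not remove it, because the text names baseline as the start of the follow-up contrast and says how the change is to be read.

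Four stronger readings are tempting, and the documents do not support them.

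- *Maintenance would be declared even if the effect had vanished.* Only that it could be: phase-wise slopes or the tabulated means might reveal the loss, and for HOPS-ST the chances above are well short of certainty.
- *The artefact can be computed from the plan.* A reader might take √0.60 = 0.77 as the baseline–outcome correlation. But the R² of 0.60 in the power paragraph is variance explained by several student and school covariates, and no selection distance is given anywhere.
- *Scores must improve without treatment.* Nomination is a teacher's overall judgment, and several outcomes (COSS-P, HPC, HPQ-T, APS, grades) are not the screen. For outcomes weakly related to it, such as grades, the artefact should be smaller, and it may be near zero.
- *There are no TAU/WL data after post-treatment.* There are: assessments after delayed HOPS, and grades for the following year, which are not restricted by arm. Neither is an untreated comparator.

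The 12-month restriction is openly stated. How many students it removes is not known. If grades were equally filled and grade 8 were always the top grade, it would be about one third.

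**Conclusion.** The point holds in limited form. Beyond about 4 months the design cannot estimate an effect versus TAU/WL, yet the exploratory sustainability analysis starts from baseline and treats the change as size of effect. In students selected for poor status, part of that change may be regression to the mean or maturation. Under the assumptions in the working, the regression part runs from about 0 to 0.35 SD with a separate baseline and from 0.12 to 0.70 SD if the baseline is the screening score. Its true size is unknown, and maturation and a possible change of teacher rater by 12 months are not included.

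The randomized post-treatment comparison is unaffected. The comparison of HOPS-ST with HOPS-RT at follow-up, already planned under Aim 3, still rests on randomization, but it cannot show that either keeps an advantage over TAU/WL. The wording should be corrected before follow-up results are reported.

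**What to change.** 1. Define maintenance as change from post-treatment to 6 and 12 months within HOPS, with confidence intervals.
2. Compute the 12-month change only in students eligible for that assessment, against their own post-treatment score.
3. Report the TAU/WL change from baseline to post-treatment beside any HOPS change from baseline, to gauge untreated improvement. It covers only about 4 months, so it does not measure later maturation.
4. State that no effect versus TAU/WL is estimated beyond post-treatment, and drop the reading of later change from baseline as size of effect.
5. Reword the follow-up expectations of Aims 1 and 2 to match. The Aim 2 sentence names HOPS-ST although that aim concerns HOPS-RT, so it needs editing in any case.

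No new data are needed and the waitlist stays as it is. The cost is a more modest follow-up claim: whether the post-treatment level is held within HOPS, not whether the advantage over usual support lasts.
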